#### 3.4.3. Stretching and Cool-Down Protocol (Approx. 5 min)

Table 3 presents an overview of the exercises designed to enhance and preserve the flexibility of muscles targeted by the primary segment of the protocol.

#### 3.4.4. Control Group Core Exercise Routine

To maintain participant engagement while ensuring minimal external variability, the control group will follow a standardized two-day-per-week abs and back exercise routine. This program does not replicate the experimental group’s structured core training but provides foundational neuromuscular activation for controlled comparisons. The routine consists of warm-up, primary exercises, and cool-down phases totaling 20–25 min per session. Specific exercise descriptions can be found in Supplementary File S1.

To guarantee minimal neuromuscular adaptation while sustaining engagement and adherence, the control group will adhere to a standardized abs and back exercise routine performed twice per week, with each session lasting approximately 20–25 min. The program encompasses a range of exercises with moderate to low intensity, focusing on the anterior and posterior trunk musculature (e.g., basic crunches, seated back extensions, static planks). However, it does not include structured progression or explosive core activation tasks. This approach intentionally avoids multi-planar, high-intensity movements, thereby allowing the protocol to function as a minimal-stimulus comparator. The objective of this study is to differentiate targeted core-specific neuromuscular adaptations elicited by the experimental protocol from general movement-based engagement. The intensity and frequency parameters were designed to ensure that the core musculature remains active at a basic functional level, without triggering measurable changes in hypertrophy, balance, or dynamic power capacity.

This controlled baseline routine has been demonstrated to enhance the interpretability of group comparisons and support internal validity by reducing confounding variability associated with total training volume or unintended adaptive responses.

### 3.5. Statistical Analysis

All statistical analyses will be conducted using IBM SPSS Statistics (version 29, IBM Corp., Armonk, NY, USA). Normality checks will be performed via the Shapiro–Wilk test (small to medium samples) supplemented by histograms, Q-Q plots, and skewness/kurtosis assessments.

Reliability Analysis:SWLS questionnaire consistency will be assessed using Cronbach’s alpha (>0.70).Item-total correlations will ensure meaningful contributions to overall scoring.

Inferential Testing:Within-group comparisons: paired samples *t*-test (normal data) or Wilcoxon Signed-Rank test (non-parametric).Between-group comparisons: independent samples *t*-test (parametric) or Mann–Whitney U test (non-parametric).Repeated-measures ANOVA will assess pre- and post-intervention changes, applying Bonferroni corrections for multiple comparisons.

Effect Size and Correlations:Cohen’s d for *t*-tests, Partial Eta Squared (η^2^) for ANOVA.Pearson’s correlation (parametric) or Spearman’s rank correlation (non-parametric) to explore variable associations.

Additional Measures:Homogeneity of variance was tested via Levene’s test.Intention-to-treat (ITT) analysis for participant dropout management, using multiple imputation techniques to mitigate bias.

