### 2.5. Sample Size Calculation

To determine the appropriate sample size for this study, a power analysis was conducted using G*Power 3.1 software [43]. The analysis was based on a repeated-measures design with two groups (experimental vs. control) measured at baseline and post-intervention. The following parameters were used: Effect Size (Partial η^2^) = 0.06 (medium effect); Cohen’s d = 0.50. Alpha Level (α) = 0.05 (5% significance threshold); power (1 − β) = 0.80 (80% probability of detecting a real effect); two measurement points (pre- and post-intervention); and two groups (experimental and control). According to the established criteria, the minimum requisite sample size for achieving adequate statistical power was computed to be 34 participants, with 17 participants allocated to each group. The objective of this study is to include and evaluate 40 participants, with 20 subjects in each group, to account for potential participant dropout. This methodological approach ensures that the study can detect meaningful differences in vertical ball strength, muscle activation (EMG), dynamic balance, angular velocity, muscle hypertrophy, and psychological impact (SWLS scores) with sufficient precision.

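### The plan lists two unranked between-group analyses, and neither uses baseline as a covariate; one ANCOVA per outcome would be more efficient and leave a single decisive test

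*Protocol article*

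**What the plan says.** Section 3.5 gives two routes to the same between-group question.

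- Route 1 is "Between-group comparisons: independent samples" t-test, or a Mann–Whitney U test where the data are judged non-parametric. The judgement follows this rule: "Normality checks will be performed via the Shapiro–Wilk test (small to medium samples"), supported by histograms, Q-Q plots and skewness/kurtosis.
- Route 2 is: "Repeated-measures ANOVA will assess pre- and post-intervention changes, applying Bonferroni corrections for multiple comparisons".

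Within-group paired t or Wilcoxon tests are listed beside these. No test is named as the main between-group analysis, and no baseline covariate appears. The section does not state whether Route 1 compares post values or changes, or which term of the ANOVA is tested. Intention-to-treat analysis with multiple imputation is planned.

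Section 3.1 has both groups measured at baseline and after the intervention. On sample size, section 2.5 says: "The analysis was based on a repeated-measures design with two groups (experimental vs. control) measured at baseline and post-intervention". It plans 40 participants, 20 per group.

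**The concern.** Two randomised groups with one baseline and one post value are the standard setting for ANCOVA of the post value on group and baseline. The listed tests use baseline either not at all or at a fixed weight of one, where ANCOVA estimates the weight. With 20 per arm that precision matters.

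The second issue is that the two routes are not ranked. On change scores, the Route 1 t-test is the same test as the 2×2 group-by-time interaction, and there is no conflict. On post values, it ignores baseline and can give a different verdict from the ANOVA. The article does not say which reading applies or which result would then decide. The Bonferroni clause is attached to the ANOVA and does not settle this.

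**Working it through.** **Inputs from section 2.5.** Effect size: "0.06 (medium effect); Cohen’s d = 0.50". Alpha: "0.05 (5% significance threshold"). Power: "0.80 (80% probability of detecting a real effect"). Minimum size: "was computed to be 34 participants, with 17 participants allocated to each group". Planned: 40. Two-sided testing is assumed. The pre-post correlation ρ is not given, so it is an assumption throughout and a range is shown.

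**Step 1: reproduce N = 34.** Take the group-by-time F test with m = 2 time points, noncentrality λ = f²·N·m/(1−ρ), and df 1 and N−2. With f = 0.25 and ρ = 0.5 at N = 34:

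λ = 0.0625 × 34 × 2 / 0.5 = 8.5, power 0.807.

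Using f = √(0.06/0.94) = 0.253 gives 0.815. N = 32 falls short for both (0.781 and 0.790), so 34 is reproduced. The between-groups factor would need 98 at ρ = 0.5, and a two-sample t-test on d = 0.50 would need 128. The figure therefore points to the interaction as the powered test, with ρ = 0.5 unstated. In a 2×2 layout f = 0.25 corresponds to a difference in change of 4 × 0.25 = 1.0 SD, not the 0.50 also quoted.

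**Step 2: variance of the group difference, relative to a post-only comparison.**

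- Post-only t-test: 1
- Change score, identical to the 2×2 interaction: 2(1−ρ)
- ANCOVA: 1−ρ²

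**Step 3: power at the planned size, d = 0.50, 20 per arm.** Noncentrality is d·√(n/2)/√(variance factor), and 0.5 × √10 = 1.581. Degrees of freedom are 38 for the t-tests and 37 for ANCOVA. The ANCOVA variance is also inflated by 1 + 1/(N−4) = 1 + 1/36 for estimating the slope. Example at ρ = 0.5: change score 1.581/√1.00 = 1.581; ANCOVA 1.581/√(0.75 × 1.0278) = 1.801.

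| Assumed ρ | Variance factor: post / change / ANCOVA | Power: post-only | Power: change or interaction | Power: ANCOVA |
|---|---|---|---|---|
| 0.3 | 1.00 / 1.40 / 0.91 | 34% | 26% | 36% |
| 0.5 | 1.00 / 1.00 / 0.75 | 34% | 34% | 42% |
| 0.7 | 1.00 / 0.60 / 0.51 | 34% | 51% | 57% |
| 0.8 | 1.00 / 0.40 / 0.36 | 34% | 68% | 72% |
| 0.9 | 1.00 / 0.20 / 0.19 | 34% | 93% | 94% |

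**Step 4: on the scale that reproduces N = 34** (1.0 SD, ρ = 0.5, N = 34). Interaction: √8.5 = 2.915, power 81%. ANCOVA: 2.915/√(0.75 × (1 + 1/30)) = 3.31, power 89%. ANCOVA reaches 80% with 28 participants.

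**Step 5: how often the routes disagree if Route 1 uses post values.** Simulation of 20,000 trials, normal data, 20 per arm, true d = 0.5: the post-value t-test and the change-score test gave different verdicts at the 5% level in about 30% of trials at ρ = 0.5 and about 40% at ρ = 0.7. With no true effect, at least one of the two was significant in about 9%.

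**Step 6: the normality switch.** Simulation of 4,000 trials, 20 per arm, ρ = 0.7, post values, with a Shapiro–Wilk test choosing between t and Mann–Whitney: type I error 0.053 (normal) and 0.052 (lognormal).

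**The case against.** The repeated-measures ANOVA is a legitimate analysis. Under randomisation its interaction is unbiased, and it matches the design behind the sample size. On the inputs that reproduce N = 34 it already has 81% power. At ρ of 0.8 or more the ANCOVA gain is small: 68% to 72%, then 93% to 94%. The article is also a condensed document, and an analysis plan not shown may name the decisive test and its covariates. All of this stands. It limits the point to the list of tests as printed and to efficiency.

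Some stronger readings are tempting but not supported:

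- **That the t-test discards baseline.** The article does not say so. On change scores it equals the interaction, so the post-only column and Step 5 apply only to the other reading.
- **That the rank route has no group-by-time counterpart.** A Mann–Whitney test on change scores is one, and it keeps the baseline information.
- **That normality checks switch the whole analysis.** The alternatives are attached to the paired and independent comparisons and the correlations, not to the ANOVA. Shapiro–Wilk is supplemented by plots and skewness/kurtosis.
- **That the switch inflates false positives.** Step 6 shows no material inflation. With lognormal data and d = 1.0, Mann–Whitney was about as powerful as ANCOVA (97% each). What remains is that the data choose both the test and the quantity estimated.

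**Conclusion.** The point holds as one of efficiency and of having a single decisive test. Two unranked between-group routes are printed, and neither adjusts for a baseline that is collected anyway. ANCOVA was at least as powerful as either route at every ρ tried from 0.3 to 0.9. Against the interaction, the gain for d = 0.50 with 20 per arm is about 10 points at ρ = 0.3, 8 at 0.5, 5 at 0.7, 3 at 0.8 and under 1 at 0.9, taken from unrounded powers. Against a post-only test it grows with ρ, from 2 points at 0.3 to 60 at 0.9.

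These figures rest on an assumed ρ, equal variances, normal data and two-sided 5% tests.

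A reader might infer that the planned ANOVA is wrong, or that ANCOVA repairs the trial's power. Neither follows. The interaction test is valid, and for d = 0.50 ANCOVA with 40 participants stays below 80% at ρ of 0.8 or below (42% at ρ = 0.5). The gap between d = 0.50 and the 1.0 SD implied by f = 0.25 is a separate sample-size question.

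**What to change.** For each outcome, name one ANCOVA of the post-intervention value on group, with that outcome's baseline value as covariate, as the decisive between-group analysis. Report the adjusted difference with its 95% CI, and fit the same model in each imputed data set.

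Keep the independent t-tests, rank tests and within-group tests as descriptive or sensitivity analyses, and say whether they use post or change values. If the repeated-measures ANOVA is kept, name the group-by-time term and label it supportive. Do not let normality checks choose the decisive test: inspect the ANCOVA residuals and, if they are badly skewed, use a log scale or a bootstrap CI for the adjusted difference. State the assumed pre-post correlation in section 2.5.

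The cost is wording and one degree of freedom; no new data are needed. The change should be made before outcomes are examined by group.

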## 2. Experimental Design

### 2.1. Trial Design

This study has been prospectively registered on ClinicalTrials.gov under the identifier AUTH-CORE-STUDY NCT07025395, ensuring transparency and alignment with international standards for interventional research protocols.

The present study protocol has also been developed and reported in accordance with the SPIRIT 2013 Statement (Standard Protocol Items: Recommendations for Interventional Trials) [39], which provides guidance for the essential content of clinical trial protocols. Furthermore, the protocol adheres to the Template for Intervention Description and Replication (TIDieR) checklist and guide [40] and the Consensus on Exercise Reporting Template (CERT) [41], ensuring comprehensive, transparent, and replicable documentation of the core training intervention.

All completed checklists (SPIRIT, TIDieR, CERT) and the ClinicalTrials.gov registration certificate are available to reviewers and readers in Supplementary File S2. The official approval letter from the Ethics Committee is provided separately in Supplementary File S3.

This study employs a two-parallel group randomized controlled trial (RCT) design. The experimental group will undergo structured core training, while the control group will continue regular physical activity without targeted interventions. Detailed descriptions of exercise parameters, progression models, training environment, and measurement techniques are provided to enhance transparency and reproducibility.

The study protocol has been reviewed and approved by the Local Ethics Research Committee of the School of Physical Education and Sport Science at Serres, Aristotle University of Thessaloniki (Approval Code: ERC-013/2025, issued on 11 March 2025), in accordance with the University’s Code of Ethics for Research Involving Human Participants, the principles of the Declaration of Helsinki [42], and the EU General Data Protection Regulation (GDPR-EU 2016/679). All participants will provide written informed consent prior to their involvement, and personal information will be handled confidentially.

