### 2.3. Eligibility Criteria

Participants for this study will be healthy, physically active adults between the ages of 25 and 35, engaging in regular recreational exercise or non-competitive sports activities. For the purpose of this study, the term “recreational exercise” was defined as physical activity engaged in a minimum of three times per week for a duration of at least one hour in each training session. A list of suitable activities is provided below, including but not limited to: aerobics, dance, folkloric dance, and swimming. A variety of outdoor activities and adventure sports are available, including orienteering, surfing, snowboarding, and caving. Racket games encompass a variety of sports, including tennis, paddle tennis, badminton, and squash. The participants were permitted to engage in a range of activities, including but not limited to mountain biking, mountain climbing, athletics, bowling, horseback riding, skateboarding, swimming, and hiking. Additionally, any other forms of exercise that the investigators deemed appropriate were permitted. In order to qualify for participation, an individual must have been continuously enrolled in the relevant programs for a minimum period of two years [41]. Inclusion is based on criteria ensuring suitability for core training interventions and reducing confounding variables related to prior structured stability training. Eligible participants must be in optimal health, demonstrating no recent musculoskeletal injuries or pre-existing conditions that could limit the full range of motion or prevent engagement in high-intensity exercise protocols. They must also commit to attending both baseline and final assessments and adhering to the structured eight-week intervention timeline to maintain data integrity.

Exclusion criteria include individuals diagnosed with musculoskeletal impairments that restrict functional movement or prevent core-specific engagement. Additionally, those with cardiovascular or metabolic conditions that contraindicate high-intensity exercise are excluded from participation. To maintain study validity, individuals already engaged in structured core training programs—such as Pilates, CrossFit, calisthenics, or athletes following systematic strength and stability regimens—will also be excluded to prevent prior training effects from influencing study outcomes.

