## 3. Procedure

### 3.1. Study Measuring Procedure

Both the experimental and control groups will undergo baseline and post-intervention measurements, scheduled at the neuromechanics laboratory of the Department of Physical Education and Sport Science, Aristotle University of Thessaloniki, in Serres. Testing sessions will be conducted by appointment, ensuring controlled environmental conditions across assessments. Upon arrival, participants’ anthropometric data—including weight, height, and age—will be recorded, alongside verification of personal contact details.

To optimize movement proficiency, participants will complete a brief warm-up routine in a designated laboratory space, ensuring sufficient joint mobility and neuromuscular readiness for the overhead medicine ball slam exercise. Following the warm-up, expert laboratory personnel will guide each subject through the measurement protocol, with a total session duration estimated between 30 and 40 min per participant.

The primary assessment will involve medicine ball overhead slam execution, during which force output will be recorded using a 3D dynamometer (Kistler, Winterthur, Switzerland) integrated with MARS performance analysis software. Simultaneously, EMG recordings will monitor muscle activation in the RA, EO, and IL, captured via bipolar surface electrodes (Biopac Systems Inc., Goleta, CA, USA). A high-definition PTZOptics Move 4K camera will document the angular velocity of the shoulder, hip, and knee joints from a standardized right-side view. To assess postural stability, participants will undergo a static balance evaluation, conducted using the Kistler 3D dynamometer while standing with eyes open. Additionally, deep-core muscle hypertrophy assessments will be performed via ultrasound imaging (Aloka ProSound SSD 3500 SV, Tokyo, Japan), measuring the TrA, IO, and LM at rest.

Psychological well-being will be evaluated using the Satisfaction with Life Scale (SWLS) questionnaire [45] to determine potential changes in the subjective quality of life resulting from the intervention.

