## 4. Expected Results

The intervention is anticipated to yield improvements in core muscle activation, particularly in the transverse abdominis, internal oblique, and lumbar multifidus, contributing to spinal resilience and segmental control. Static balance is expected to improve via enhanced neuromuscular coordination and recruitment efficiency, while higher force outputs are projected during medicine ball slam trials, indicating improved motor control and kinetic chain engagement. Beyond musculoskeletal outcomes, the intervention is expected to elicit beneficial neural and metabolic adaptations. These may include enhanced intermuscular coordination, improved regulation of joint angular velocity, and increased corticospinal excitability—factors that collectively contribute to more efficient motor unit recruitment and refined movement control. Furthermore, the application of core bracing techniques may facilitate intra-abdominal pressure modulation, enhance spinal stability, and lead to improved task-specific energy efficiency during dynamic full-body movements. These neuromechanical enhancements are anticipated to play a central role in the observed performance and balance improvements.

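### The only outcome-to-outcome analysis in section 3.5 is a bivariate correlation that does not condition on randomised arm, so a training effect alone can create associations if the arms are pooled

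*Protocol article*

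**What the plan says.** Section 2.1 sets the design: "This study employs a two-parallel group randomized controlled trial (RCT) design". For associations between outcomes, section 3.5 offers Pearson's correlation for parametric data or Spearman's "rank correlation (non-parametric) to explore variable associations". It does not say which pairs, which time point, raw or change values, or whether the arms are pooled. The article contains no partial correlation, regression, mediation model or within-arm analysis. The Bonferroni correction in the same section is attached to the repeated-measures ANOVA.

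Section 4.6 expects the trained arm to do better on activation, force, balance, muscle thickness and life satisfaction. Section 3.4.4 designs the control routine so that it should not measurably change hypertrophy, balance or power. Section 4 adds an expectation about how the outcomes relate: "These neuromechanical enhancements are anticipated to play a central role in the observed performance and balance improvements".

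**The concern.** In a two-arm trial whose treatment is meant to move many outcomes at once, the pooled sample consists of two clusters. A bivariate coefficient across both clusters mixes two things: the association between outcomes among people treated alike, and the distance between the arm means. Only the first says anything about whether a person who gains more thickness also gains more force. The second merely repeats that training affected both outcomes, which the randomised comparison already shows.

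At stake is the reading of the exploratory results. A thickness-force or EMG-force coefficient could reach significance with no association inside either arm. No other planned analysis would show that.

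**Working it through.** **Inputs from section 2.5.** Partial eta squared 0.06, also given as Cohen's d = 0.50; alpha 0.05; power 0.80; two groups, two time points; minimum 34 (17 per arm); target 40 (20 per arm). The within-person correlation rho is not given. I assume 0.5 and two-sided tests.

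**Step 1: reproduce the plan's figure.** For the group-by-time interaction, lambda = f² × N × m / (1 − rho). With f = 0.25, N = 34, m = 2 and rho = 0.5, lambda = 0.0625 × 34 × 2 / 0.5 = 8.5, and power is 0.807. With f = √(0.06/0.94) = 0.253, power is 0.815. The minimum N is 34 in both cases, so the stated figure reproduces.

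**Step 2: the arm difference this implies on change scores.** With two time points, the interaction test is a t-test on changes, whose squared noncentrality is d² × n/2 with n per arm. Setting d² × 17/2 = 8.5 gives d = 1.0. So 17 per arm at about 80% power corresponds to an arm difference of about 1.0 SD of change. Given that N and power, this does not depend on rho.

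**Step 3: the correlation induced by pooling.** Take two equal arms and two outcomes unrelated within arm, each shifted by d SD. Then pooled r = (d²/4) / (1 + d²/4).

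- d = 0.5: 0.0625 / 1.0625 = 0.06
- d = 1.0: 0.25 / 1.25 = 0.20
- d = 1.5: 0.5625 / 1.5625 = 0.36

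**Step 4: how often this is called significant.** At N = 40 the critical |r| is 0.312, and at N = 34 it is 0.339. The table gives results from 40,000 simulated samples per row, using the Pearson test.

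| Arm difference in both outcomes | Induced r | p < 0.05, unadjusted, N = 40 | Adjusted, N = 40 | Unadjusted, N = 34 |
|---|---|---|---|---|
| 0 | 0 | 5.2% | 5.1% | 4.9% |
| 0.5 SD | 0.06 | 6.6% | 5.1% | 6.5% |
| 1.0 SD | 0.20 | 24% | 5.1% | 21% |
| 1.5 SD | 0.36 | 67% | 4.8% | 60% |

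The adjusted column is a partial correlation given arm and one further binary factor that has no effect in these rows. Spearman's coefficient was not simulated, but it is bivariate too.

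**Which values this covers.** The calculation applies to change scores and, in kind, to post-intervention values. Pooled baseline values carry no training effect and so escape it. If training shifts only one of the two outcomes, the induced correlation is zero.

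**The case against.** The strongest reply is that the article does not commit to pooling. Pairs, time point and stratification of an exploratory step are details that a condensed article may leave to a fuller document, and either coefficient could be computed within each arm without contradicting section 3.5. That stands as a limit: the figures are conditional on pooling. It does not remove the point, because the named methods cannot themselves condition on arm and an arm-respecting analysis is available at almost no cost.

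A second reply is that 24% needs a 1.0 SD effect, while section 2.5 prints d = 0.50, which would give 6.6%. Both belong in the range. The larger value is what the sample size can detect on change scores; if the effect is nearer 0.5 SD, little is lost.

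Three stronger readings are tempting, and the documents do not support them.

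- **Sex and body size make most of these correlations spurious.** Eligibility reads "Participants for this study will be healthy, physically active adults between the ages of 25 and 35" and never mentions sex, so a mixed-sex sample is an inference. No sex or size effects are given. With an assumed 50:50 split and assumed sex differences of 0.5, 1.0, 1.5 and 2.0 SD in both outcomes, the rates at N = 40 are 6.4%, 24%, 67% and 96%. The answer is therefore set by the assumption, and change scores would largely remove such stable differences.
- **Dozens of uncorrected tests.** The plan describes no all-against-all matrix, so a count of pairs cannot be charged to it.
- **A wrong mechanistic conclusion.** Section 3.5 presents the correlations as exploratory, none of the five hypotheses at the end of section 1.3 concerns an association between outcomes, and the section 4 expectation is not tied to them. How a later paper would read them is a prediction.

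**Conclusion.** The point holds in a limited form. The only method named for relating outcomes to each other ignores the randomised arm. If the arms are pooled on change scores, a treatment effect of the size the trial can detect (about 1.0 SD in both outcomes) raises the chance of a significant coefficient between outcomes unrelated within arm from 5% to about 24% at N = 40. At 0.5 SD the rise is only to 6.6%.

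The result rests on pooling, equal arms, equal shifts in both outcomes and no within-arm association. It concerns a secondary, exploratory step and leaves the randomised comparisons, the five hypotheses and the sample size untouched. It is a minor point, worth correcting because the correction is nearly free.

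**What to change.** Add to section 3.5 that associations between outcomes will be computed on pre-to-post changes as partial correlations, or equivalent regressions, adjusted for randomised arm. Add body mass as a covariate where force or thickness is involved. It is already available, since section 3.1 states that "anthropometric data—including weight, height, and age—will be recorded". Add sex if it is recorded; sections 2.6 and 3.1 do not list it. Report estimates with 95% confidence intervals, and state that they are exploratory and not evidence of mechanism.

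The cost is one to three degrees of freedom (from 38 for a bivariate correlation at N = 40 to between 37 and 35), and smaller coefficients wherever the arm difference had inflated them. Apart from sex, no new data are needed.
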